# Chapter Four

# Study Methodology

## 4.1 Study site and population

The study will be done in the two districts of Masindi and Kiryandongo in western Uganda, 214 kilometres northwest of Kampala the capital city of Uganda. It is bordered by Amuru district in the north; Oyam to the northwest; Apac in the South; Hoima to the southwest and Bulisa in the Northwest. It is administratively divided in to three counties (Buruli, Kibanda and Bujenje); eight sub counties and 40 parishes. The district population is projected to be 603,000 inhabitants by 2010, 50.9% being male and 49.1% female. Its inhabitants are of heterogeneous ethnicity and nationality; the Banyoro comprising about 59%. The population is predominantly rural with about 5.43% being urban. It has a population density of 124 per square kilometres.

There are two general Hospitals and one sub district hospital, Masindi, Kiryandongo and Bwijanga respectively; 16 health centre III levels and; 26 health centre II levels (Masindi having 25 health centres while Kiryandongo has 17. In this region ANC new attendance is 89.4%; ANC fourth visit is 29.4%; IPT_2_ at 27.2% and Health facility deliveries in this region is 23.5% ([DHO 2010](#_ENREF_28)).

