### 4.4.9 Sampling procedure

Sixteen health centres in total will be proportionally selected from both Masindi and Kiryandongo district with Masindi contributing to 10 and Kiryandongo contributing to 6 HCs. A community trail involving two arms will be tried.

*Selection of the experimental units (pregnant women)*

Ten and six health centres will be proportionally selected from Masindi and Kiryandongo district giving a total of 16 heath centres in the trail.

From the 16 selected health centres, 8 of these will be purposively assigned to each of the two arms to minimize contamination. In each of the 8 health centres on each trial arm, 868 pregnant women with 28 weeks of pregnancy or below will be enrolled as they come in giving a total of 1736 in this trial. Health centres on two extremes of the districts will be assigned to either the intervention or the control group in order to avoid contamination between the two.

*Data Collection tools and procedures*

Semi-structured questionnaires written in English but administered in Runyoro will be used by research assistants.

*Training of research assistants*

Data collectors will be recruited and trained on data collection methods for two days. Training will include how to conduct individual interviews and data collection skills

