# 5.1 Study limitations

1. This study focuses on prenatal mothers attending ANC services at the primary healthcare centres; systematically excluding the 5-10% of pregnant women who may not make any prenatal contact with the health facilities during the current pregnancy.
2. Some pregnant women make first ANC visit late in the third trimester, the primary target for this study are pregnant women reporting with gestation age of up to 28 weeks. For limitations one and two different intervention strategies are required to target this category of pregnant women who may have their peculiar needs different from the ones targeted by this study.
3. The risk of contamination across the study arms -this will be minimised by purposively allocating health centres in the extremes of the districts to either of the two arms.

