## Annex 10: List of eligible Health Centres by HSD

| **S/N** | **HSD** | | |  |
| --- | --- | --- | --- | --- |
|  | **Buruli** | **Bujenje** | **Kibanda** |  |
| 1 | Kimengo | Budongo | Mutunda |  |
| 2 | Kilanyi | Ikoba | Diika |  |
| 3 | Pakanyi | Nyantonzi | Panyadoli |  |
| 4 | Nyakitibwa | Mihembero | Diima |  |
| 5 | Kyatiri | Ntooma | Karungi |  |
| 6 | Kigezi | Bwijanga | Kigumba |  |
| 7 | Kibwona | Kikingura | Katulikire |  |
| 8 | Kijunjubwa | Nyabyeya | Apodorwa |  |
| 9 | Kitanyaata | Kyamaiso | Mpuumwe |  |
| 10 | Kijenga | Kisalizi | Masindi port |  |
| 11 | Kibyamu |  |  |  |
| **Totals** | **11** | **10** | **10** | **31** |

| Annex 14: Budgetsi) Budget Sub study one: Assessing the primary health care workers' knowledge-base and perceptions about educational interventions during ANC clinics | | | | | | | | | | |
| --- | --- | --- | --- | --- | --- | --- | --- | --- | --- | --- |
| **Phase** | | **Activity Detail** | | **Number of Officers** | **Rate** | | **Number of days** | | **Totals** | |
| **Preparatory Phase** | | IRB costs | | 1 | 600,000 | | 1 | | 600,000 | |
|  |  | Uganda National Council of Science & Technology | | 1 | 720,000 | | 1 | | 720,000 | |
|  |  | Identify and Constitute Research Team Assistants etc | | 1 | 30,000 | | 1 | | 30,000 | |
|  |  | Per diems for Research Assistants | | 5 | 60,000 | | 10 | | 3,000,000 | |
|  |  | Per diems for Researcher | | 2 | 90,000 | | 10 | | 1,800,000 | |
|  |  | Training of Research Assistants | | 5 | 60,000 | | 3 | | 900,000 | |
|  |  | Pretesting of Study tools | | 1 | 100,000 | | 2 | | 200,000 | |
|  |  | Correction & Assembly of necessary study tools | | 200 | 300 | | 1 | | 60,000 | |
| **Field Costs** | | Local Car hire | | 2 | 80,000 | | 10 | | 1,600,000 | |
|  |  | Car Hired from Kampala | | 1 | 150,000 | | 12 | | 1,800,000 | |
|  |  | Fuel to and from Kampala | | 1 | 200,000 | | 2 | | 400,000 | |
|  |  | Fuel for Local field Travels | | 3 | 50,000 | | 10 | | 1,500,000 | |
| **Data Handling** | | Data entry & Cleaning | | 2 | 350,000 | | 7 | | 4,900,000 | |
|  |  | Data analysis | | 1 | 2,000,000 | | 1 | | 2,000,000 | |
|  |  | Manuscript writing | | 1 | 150,000 | | 1 | | 150,000 | |
| **Dissemination,**  **Manuscript writing and Publication** | | Discussions of results with District Officials | | 20 | 10,000 | | 2 | | 400,000 | |
|  |  | Discussion of results at the School of Public Health | | 1 | 100,000 | | 1 | | 100,000 | |

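### Health centres are assigned to arms by location and without randomisation, so any prior difference between locations is read as the intervention effect

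*Protocol*

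**What the plan says.** Protocol section 4.4.9 takes 16 health centres from the two districts, "with Masindi contributing to 10 and Kiryandongo contributing to 6 HCs". It then says: "From the 16 selected health centres, 8 of these will be purposively assigned to each of the two arms to minimize contamination". The basis is geographic: "Health centres on two extremes of the districts will be assigned to either the intervention or the control group". Section 5.1 gives the same rule as the answer to contamination: "this will be minimised by purposively allocating health centres in the extremes of the districts to either of the two arms". Confounding by location is not among the limitations there.

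No random allocation of centres appears in sub-study three. Sections 3.7 and 4.4.2 nevertheless set out to measure the effect of the package, and section 4.4.8 uses a published formula for cluster-randomised trials.

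Section 4.4.10 runs cross-tabulations and chi-square tests, then carries into a logistic model whatever was significant at that step. It names no centre-level baseline. Annex 10 lists 31 eligible centres: 11 in Buruli, 10 in Bujenje and 10 in Kibanda.

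**The concern.** When the investigator assigns arms by place, place and treatment cannot be told apart by design. Suppose women at one end already deliver in facilities more often, for reasons unrelated to the trial. The arm comparison then contains that difference in full. It could show an effect where there is none, or hide a real one, and this applies to every primary outcome.

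The analysis is not set up to correct for it. Choosing covariates by bivariate significance does not ensure that the ones separating the two locations enter the model. With 16 centres, an important imbalance can easily fail such a test.

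The protocol gives some reason to expect local differences. Of the study population, section 4.1 says: "Its inhabitants are of heterogeneous ethnicity and nationality". Section 1.4 describes newborn care practices as rooted in culture. Neither section says that these features run from one end of the area to the other, so this is a plausible route to confounding and not evidence of it.

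**Working it through.** **1. The plan's own sample size.** Inputs from section 4.4.8: design effect D = 2.5, Z values 1.96 and 0.84, π0 = 0.235, π1 = 0.335, 10% loss.

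n = D(1.96 + 0.84)²[π0(1−π0) + π1(1−π1)]/(π0 − π1)²
= 2.5 × 7.84 × (0.179775 + 0.222775)/0.01
= 789.0 (stated: 788).

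789.0 × 1.10 = 868, as stated. The denominator is printed with a plus sign, but only the minus sign reproduces the figure. Changing how centres are allocated leaves 868 per arm as it is.

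**2. How far arm and location coincide.** With 10 and 6 centres and 8 per arm, arm cannot equal district: if all 6 Kiryandongo centres went to one arm, 2 from Masindi would have to join them. The text does not say whether opposite ends are taken within each district or across both. Across both, the bias is the gap between the two ends. Within each district, and supposing a 5:5 and 3:3 split, it is (5 × Masindi gap + 3 × Kiryandongo gap)/8. Neither is zero by design.

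**3. What an assumed gap would do.** The documents give no figure, so gaps of 0, 2, 5 and 10 points are assumptions. The simulation had 20,000 runs with no intervention effect. There were 8 centres at each end and 98 women followed per centre (788/8 = 98.5). The base rate was 23.5% and the coefficient of variation within each end was 0.25. The test was an unpaired t-test on centre proportions at 5%. This test respects clustering, so the inflation comes from location alone.

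| Assumed gap | Bias, by location | False positives, by location | Bias, randomised | False positives, randomised |
|---|---|---|---|---|
| 0 | 0.0 | 5.2% | 0.0 | 4.9% |
| 2 points | 2.0 | 7.8% | 0.0 | 5.0% |
| 5 points | 5.0 | 21.5% | 0.0 | 5.1% |
| 10 points | 10.0 | 59.5% | 0.0 | 4.9% |

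The randomised columns use a simple random split of the 16 centres. A normal approximation with D = 2.5 and 788 per arm gives standard errors of 0.0343, 0.0349 and 0.0357 for gaps of 2, 5 and 10 points, and rejection rates of 9%, 30% and 80%. The direction is the same. The exact rate depends on how clustering is represented.

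**4. Is there room to randomise?** A split balanced within district still allows C(10,5) × C(6,3) = 252 × 20 = 5,040 allocations. On the population and density in section 4.1, the area is 603,000/124 ≈ 4,863 km². For 16 centres that is about 304 km² each, or an average spacing of √304 ≈ 17 km. For all 31 it is about 157 km² each, or 12.5 km. These are averages only; the protocol gives no map, distances or catchment boundaries.

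**The case against.** **Contamination is a real reason for separating the arms.** It might be inferred that separation is unnecessary because the education team works at the facility. The documents do not support that. Under Annex 15 (ii) the phones belong to CHWs who live in the community, section 4.4.1 has reminders reaching women at home through them, and Annex 15 (iii) adds field visits by the Health Assistant. Spillover between neighbouring catchments is possible, and randomising spaced centres carries somewhat more of it than opposite ends would. This stands as a cost of the fix. It does not show that location must decide the arm.

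**Useful covariates are already recorded.** The enrolment procedure in Annex 15 (i) notes ethnicity, parity, distance, earlier ANC attendance and earlier place of delivery, and section 4.4.10 intends to control confounding. This helps in part. However, it is not explicit that the control arm uses that procedure, and section 4.4.10 selects covariates by significance. A separate analysis plan could improve the model, but the allocation is fixed here and no model fully undoes it.

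**The protocol calls this a community intervention trial.** Sub-study three does not describe its own allocation as random; only the formula comes from that setting. A reader might conclude that the formula should go. It should not: the design effect and k describe clustering, which is present however the centres are assigned.

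**Feasibility is not shown.** Without a map, non-adjacent catchments are plausible but unproven. If Kibanda is Kiryandongo (an assumption), 6 of its 10 listed centres are used and only 4 are left as buffer.

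**Conclusion.** The point holds and should be settled before centres are assigned. Arm is tied to location by design, no baseline correction is fixed in the protocol, and section 5.1 does not acknowledge the problem. Any gap between the locations enters the estimate in full.

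The size of that gap is unknown. The rates of about 8%, 22% and 60% show what assumed gaps of 2, 5 and 10 points would do; they do not predict this trial's error rate.

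Three stronger readings are not supported:

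- A reader might derive a gap from k = 0.25, since 0.25 × 23.5 gives a between-centre SD of 5.9 points, part of which could be placed between the two ends. Section 4.4.8 defines k as variation among clusters belonging to one group. A gap between the arms' locations would come on top of it.
- A reader might infer that staffing and distance are stated to differ between the two ends. The percentages of posts filled and of people living near a facility (sections 1.5 and 3.2 and the Ugandan perspective under 1.1) are not broken down by location within the study area.
- A reader might take arm to be the same as district. The numbers of centres rule that out.

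**What to change.** **Allocation.** From the 31 centres in Annex 10, choose 16 (10 Masindi, 6 Kiryandongo) with non-adjacent catchments as far as the map allows. Then randomise 5:5 in Masindi and 3:3 in Kiryandongo. Replace the purposive rule in sections 4.4.9 and 5.1 accordingly.

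**Adjustment, whichever allocation is used.** Name the covariates of the primary model in advance and do not pick them by bivariate significance. Use what Annex 15 (i) already records (previous ANC attendance, previous place of delivery, ethnicity, distance), collected the same way in both arms. Add each centre's baseline ANC and delivery rates from routine records where these exist. Delivery counts at a centre are an imperfect baseline, because the outcome counts delivery in any formal facility.

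**If purposive allocation is kept.** Describe and report the study as a non-randomised controlled comparison, and add confounding by location to section 5.1. Keep the design effect and k in the sample size.

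**Cost.** One random draw before the start, a check of the 16 catchments on a map, and extraction of routine counts for 16 centres. Numbers of women, centres, teams and phones stay the same. The price is somewhat more contamination risk than with opposite ends, which the spacing limits.

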In Uganda there is the on-going work on the “Uganda Newborn Survival Study” in the Iganga-Mayuge Demographic Surveillance Sites (DSS), under the stewardship of Makerere University School of Public Health in collaboration with *Karolinska Institutet* ([Waiswa P 2010](#_ENREF_96)). It explored newborn care practices in communities and the formal healthcare system making major revelations: low uptake of newborn care practices in the homes especially among the poorer segments of communities, delay in seeking for care associated with delays in recognition of symptoms and homecare practices that are potentially harmful to the newborn. These findings provide us with relevant information on what to do, but does not tell us *how to do it.*

Available data about the prevalence and determinants of potentially harmful newborn homecare practices ([Byaruhanga R, Nsungwa-Sabiiti et al. 2010](#_ENREF_15); [Waiswa P 2010](#_ENREF_96)) in Uganda, point to care practices being deeply rooted in culture and beliefs.

These studies recommend that to effect change in behaviour requires interventions early in pregnancy. However, the study by Waiswa et al ([Waiswa P, Stefan P et al. 2010](#_ENREF_99)), was conducted in a small and homogenous population of the DSS compromising generalizability of its results.

In part, this study aims to collect data on prevalent homecare practices (maternal nutrition for pregnant women; thermal care, care for the cord and pre-lacteal feeds for the newborn) and their rationale among an ethnically diverse (multi-lingual, multi-national) population of Masindi and Kiryandongo districts; identify harmful practices to be discouraged and healthy ones that can be promoted.

This study seeks to identify challenges with delivering prenatal educational interventions at the primary care facility; assess the rationale for homecare practices in the community and use these findings to design and deliver tailored educational intervention to suit individual needs for pregnant women visiting ANC clinics. This approach will ensure appropriate and focused prenatal messages with the potential to achieve timely return ANC visits, institutional deliveries, improved prenatal and newborn homecare practices, ultimately contributing to the reduction in maternal and neonatal mortality.

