## 4.3.8 Data collection and analysis plan

For both qualitative and quantitative data collection techniques research assistants familiar with the local dialect (Runyoro, Luo and Kiswahili) and possessing at least a degree in social sciences or public health having experience in social research will be recruited and trained for three days on the use of available tools and techniques. Pre-testing will be done twice to ensure suitability of the tools. Qualitative data from the Key Informant Interviews with elderly caregivers, TBAs and lactating women will be audio taped, transcribed verbatim and translated in to English, themes regarding prenatal and newborn homecare practices will be identified and described. A detailed description of the different care practices will be explored from elderly care givers and TBAs; these practices will be elaborated and broadly categorised according to prenatal, intra- and post-natal periods. The computer software program NVivo will be used. We will use content analysis to analyse data from TBAs and elderly caregivers and lactating mothers. Analysis will focus on making a detailed description of maternal and newborn care practices and the rationale for these care practices in the homes. For the In-Depth Interviews manual analysis of experiences of the different age groups adolescents (young adolescent ages 10-13 years; middle age 14-16 years and older adolescents ages 17-20) and older women over 20 years will be considered.

In the quantitative data with lactating mothers research assistants will be recruited and trained on the use of data collection tools; questionnaires will be pre-tested twice to ensue suitability of data collection tool; double data entry will be done in *epidata version 3.02*, cleaned and exported to *stata version 10.0* for analysis. Results will be presented in terms of descriptive statistics in proportions and rates. In a second level using bivariate data analysis, we will test for association between socio-demographic characteristics and the different maternal and newborn care practices using odds ratios and confidence intervals to test for levels of significance.

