### 4.4.6 Inclusion and exclusion criteria:

*Inclusion:*

All pregnant women found to be up to 28 weeks of pregnancy in Masindi and Kiryandongo districts registered for ANC in the 16 selected health centres will be eligible participants. Gestational age will be estimated using the Last Normal Menstrual Period (LNMP) as volunteered by the pregnant woman and verified by palpation of height of fundus.

Pregnant women sampled for inclusion in to the study will be followed until one month after the termination of pregnancy and they will be assessed for the primary outcomes of interest: **i)**  *timely return ANC visits* **ii)** *completed four ANC visits*, **ii)** *institutional deliveries* and **iii)** *homecare practices for newborns*. The end point for the follow-up of study participants will be up to four weeks after termination of pregnancy (the neonatal period).

Although early initiation of ANC in the first trimester is known to allow sufficient time for delivering repeated educational messages, the gestation age of 28 weeks has been purposely chosen because a significant proportion of women (about 45%) in this region of Masindi and Kiryandongo make their first ANC visit in the second trimester ([DHO 2010](#_ENREF_28)).

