- Immunisation of the child, polio 0, BCG etc.

- Recognition of a sick child-hot to touch, refusing to feed, crying unusually,

All these information should be derived from discussions with the pregnant woman-not as a set of instructions to be strictly followed-compromises should be made at every stage-all that is agreed upon should be detailed down in the file. The counsellor should moderate the discussions, if the pregnant woman has come with a partner or a caretaker; both of them should be involved in the discussions even if the care taker is not pregnant-if there is a caretaker present then this should be recorded and state the relationship between them.

Tick the areas that were discussed, mark with a cross what you did not discuss with her, note down important decisions that you have agreed upon with the participant-you will use this as a reference point in subsequent meetings and discussions

Ensure that the discussion does not exceed 30 minutes unless there is expressed interest from the participant to continue. And this expression should be noted down in the file.

For subsequent visits indicate appointment dates and actual revisit dates

Later on follow-up for delivery and record where she has delivered from

Assess for the different practices outlined annex 6 will be used to assess the following outcomes

Place of delivery, Cutting of the cord, care for the cord, initiation of breast feeding, provision of pre-lacteal feeds, in case of illness how it was recognised, what action was taken, how soon was the care seeking from onset of disease or when the decision was made that the child was unwell, what facility did she take the child, outcome, at the periphery of assessment the researcher will want to know whether the child is still alive just at one month.

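### Runyoro is the only interview language named for the trial questionnaires, although the protocol describes a multi-lingual population and plans three languages for sub-study two; interview-based outcomes may be mis-measured

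*Protocol*

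**What the plan says.** For the trial (sub-study three), section 4.4.9 states: "Semi-structured questionnaires written in English but administered in Runyoro will be used by research assistants". Sections 4.4.9 and 4.4.10 mention no interpreter and no version in another language.

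The population is described differently elsewhere. Section 4.1 says: "Its inhabitants are of heterogeneous ethnicity and nationality; the Banyoro comprising about 59" per cent. Section 1.4 speaks of an "ethnically diverse (multi-lingual, multi-national) population of Masindi and Kiryandongo districts".

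For the household survey in the same two districts (sub-study two), section 4.3.8 asks for "research assistants familiar with the local dialect (Runyoro, Luo and Kiswahili").

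Three further statements bear on the point:
- Eligibility in section 4.4.6 is set by gestation and registration ("All pregnant women found to be up to 28 weeks of pregnancy in Masindi and Kiryandongo districts registered for ANC"). Neither the inclusion nor the exclusion criteria mention language.
- The first procedure in Annex 15 says: "Assess for the different practices outlined annex 6 will be used to assess the following outcomes". The list that follows includes place of delivery, cord care and start of breastfeeding. Annex 6 is the sub-study two questionnaire for lactating women.
- On allocation, section 4.4.9 says: "Health centres on two extremes of the districts will be assigned to either the intervention or the control group". Section 5.1 repeats that this is purposive.

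**The concern.** The same questionnaire is to be used on much the same kind of respondent in the same districts. It is planned with three languages for the formative survey and one for the trial. Nothing explains the narrowing, and section 5.1 does not list it as a limitation.

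Newborn care practices are one of the four primary outcomes in section 4.4.1, and they are obtained by asking the mother. A woman interviewed in a language she does not command may misunderstand questions on cord care, drying, wrapping or bathing. Misclassification of a yes/no outcome pulls a true difference between arms towards zero when it is equal in both arms. When it is unequal it can create or mask a difference. Allocation is purposive and geographic, so nothing in the design balances the language mix between arms.

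Detecting the problem afterwards would be hard. Annex 6 records neither ethnicity nor interview language. Ethnicity is among the file details in Annex 15, but that item sits in the procedure for the educational intervention, so its collection in the control arm is not certain.

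**Working it through.** **Comparing the two sub-studies**

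| | Sub-study two | Sub-study three (trial) |
|---|---|---|
| Languages named | Runyoro, Luo, Kiswahili (4.3.8) | Runyoro (4.4.9) |
| Questionnaire | Annex 6 (4.3.6) | Annex 6 for delivery and newborn outcomes (Annex 15) |
| Training of assistants | three days (4.3.8) | two days (4.4.9) |
| Pre-test | twice (4.3.8) | one day, a few health centres (4.4.10) |

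**Upper-end proxy for the women affected**

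Non-Banyoro share: 1 − 0.59 = 0.41. If enrolment mirrored the district, that is 0.41 × 868 = 356 women per arm and 0.41 × 1,736 = 712 in total. If half of them could answer in Runyoro (an assumption), the share is 0.205 and the total is 0.205 × 1,736 = 356.

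**Model for the effect on a yes/no outcome**

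Let p be the true prevalence and L the share interviewed in a language they do not command. Among those women let Se and Sp be the sensitivity and specificity of the answer. Then

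observed = (1 − L)p + L[Se·p + (1 − Sp)(1 − p)].

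The document gives none of L, Se and Sp. I assume Se/Sp of 0.80/0.95, 0.80/0.80 and 0.70/0.90. For p I use 42%, the good-cord-care figure in section 4.3.5.

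**Equal language mix in both arms**

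With no true effect the spurious difference is zero. A true difference is multiplied by 1 − L(2 − Se − Sp). For a true 10 points (42% against 52%):
- L = 0.41, Se/Sp 0.80/0.95: 1 − 0.41 × 0.25 = 0.8975, so 9.0 points are observed.
- L = 0.41, either other pair: 1 − 0.41 × 0.40 = 0.836, so 8.4 points.
- L = 0.205: 1 − 0.205 × 0.25 = 0.949 and 1 − 0.205 × 0.40 = 0.918, so 9.5 and 9.2 points.

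**Unequal language mix, no true effect**

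The spurious difference is (L₂ − L₁) × [(1 − Sp)(1 − p) − (1 − Se)p]. At p = 0.42 the bracket is −0.055, +0.032 and −0.068 for the three pairs.

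| Share in the two arms | Spurious difference, points |
|---|---|
| 41% and 41% | 0.0 |
| 31% and 51% | −1.1, +0.6, −1.4 |
| 21% and 61% | −2.2, +1.3, −2.7 |

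For self-reported place of delivery, with p = 23.5% (section 4.4.8), the brackets are −0.00875, +0.106 and +0.006. A 31%/51% split then gives −0.2, +2.1 and +0.1 points.

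The sign changes with the assumed type of error, and the size scales with an imbalance that the document does not report.

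**The case against.** The strongest reply is that section 4.4.9 names one language without forbidding others. Women are enrolled as they come, and multilingual assistants could adapt. Annex 6 is also the tool that the three-language assistants administer in sub-study two, and the one-day pre-test in both districts could reveal a language problem. This has some force: the text does not say that non-speakers will be turned away or left out, and that should not be claimed. But the stated rule is Runyoro, and leaving the rest to improvisation is what a protocol should avoid.

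Second, ethnicity is not language. A reader might infer that 41% of participants will be mis-measured. The documents do not support that: section 4.1 gives an ethnic share, and no section says how many women cannot be interviewed in Runyoro.

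Third, a reader might infer that outcomes will be mis-measured unevenly between arms, or attach a definite bias such as 3 points (a 20-point imbalance times a 15-point understatement, 0.20 × 0.15). No language or ethnicity data are given by health centre or arm, and both factors are invented. Geographic allocation makes imbalance possible, not established. The root of any uneven error would be that allocation, with interview language as the route.

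Fourth, the reach is limited. Antenatal visit outcomes rest on appointment and revisit dates written in the file. Place of delivery is a simple fact that staff are told to follow up and record. This objection stands, and it narrows the point mainly to newborn practices.

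**Conclusion.** The inconsistency is real: one interview language for the trial, set against a population the protocol calls multi-lingual and three languages for the same questionnaire in the same districts. Followed as written, the plan may worsen measurement of newborn practices, and of place of delivery where it is self-reported, among women who do not command Runyoro.

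The number of such women is unknown, and 41% is an upper-end proxy. With an equal language mix and equal error rates the consequence is dilution: a true 10-point difference appears as 8.4 to 9.0 points at a 41% share, and 9.2 to 9.5 at half that, under the assumed error rates. A difference in error between arms is possible because of the geographic allocation, but its size and direction cannot be determined from the document. No sample size or power figure in section 4.4.8 depends on this point. It is worth correcting because the correction is cheap, not because a bias has been demonstrated.

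**What to change.** Change the data-collection statement in section 4.4.9 so that trial questionnaires are administered in Runyoro, Luo or Kiswahili by language-matched research assistants in both arms, in line with section 4.3.8. Include the three versions in the pre-test already planned in section 4.4.10. Add one item recording the interview language for each woman, so that the mix can be compared between arms. If Runyoro alone is intended, say so and list it among the limitations in section 5.1.

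The cost is preparing and pre-testing two further language versions. Section 4.3.8 requires assistants who know the three languages but does not say that written translations exist, so this work should not be assumed already done. Recruiting assistants with these languages is already foreseen for sub-study two.
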